***collabo****RATE****.***
**collabo**RATE is a three-item, patient-reported experience measure of how patients perceive the effort that clinicians make to achieve three core aspects of shared decision making: informing patients, eliciting preferences, and integrating preferences into decisions made [27, 34]. Patients answer each question on a scale of 0 to 9. The measure is scored by using the percentage of patients who give the highest possible score of 9 for each item (top score) [27, 34].*Uterine Fibroid Symptom and Health-Related Quality of Life Questionnaire (UFS-QOL) symptom severity subscale.* We will ask patients to complete only the symptom severity subscale portion of the 37-item UFS-QOL questionnaire. The eight-item subscale asks patients how distressed their symptoms have made them feel over the past 3 months [35]. Each item is scored on a Likert-type scale from “1” (none of the time) to “5” (all of the time) [35].*The Comprehensive Score for financial Toxicity (COST).* COST is a patient-reported outcome measure to assess financial toxicity in patients with cancer [36, 37]. The measure contains 11 items. Study stakeholders, including patient partners, felt that the majority of the items were not applicable for this study and wanted to minimize respondents’ burden; therefore, we opted to only use one item. The question reads: “I worry about the financial problems I will have in the future as a result of my illness or treatment”, and the response scale is from “0” (not at all) to “4” (very much).*Chew Health Literacy Measure.* Three-item validated measure of health literacy. The items are the following: How confident are you filling out medical forms by yourself? How often do you have someone (like a family member, friend, hospital/clinic worker, or caregiver) help you read hospital materials? How often do you have problems learning about your medical condition because of difficulty understanding written information? Patients who circle “extremely” or “quite a bit” on the Likert-type scale are considered to have high health literacy [38].*Resource utilization (ambulatory and hospital).* The follow-up survey will query eligible patients to self-report the number of outpatients (or visit to primary care clinician), inpatient, or emergency visits during the 3-month follow-up period.*Treatment choice.* Patients will identify their intended treatment choice in the post-encounter survey. We will also ask patients in the 3-month follow-up survey whether they have seen another clinician about another treatment, whether an Option Grid tool was used in that encounter, and to identify the final treatment option they selected, or will select if they proceed with scheduling the treatment intervention.*Patient demographics*. We will collect the patient’s email address, health insurance status, age, race, gender, and spoken language via the survey they complete on the tablet computer post-encounter.

### Procedure

The implementation procedure was guided by CFIR’s inner setting and its related constructs (see Additional file 3 for details).

#### Clinician consent

Dartmouth project staff met with clinicians at each site in January and February 2019 to introduce the project. Co-investigators and stakeholder partners at each site will help identify clinicians who are eligible to participate in the study prior to the start of their pre-implementation phase and ahead of their second site visit. Prior to the second site visit, the principal investigators at each site will receive an information sheet describing the aims and methodology of the study via email. They will disseminate the information sheets to eligible clinicians. Eligible clinicians who wish to participate can provide their written consent in-person during the project staff’s second site visit, email their consent forms to the project staff at their earliest convenience, or return them to project staff at each site. Clinicians can opt-in on the consent form to have a sample of 10 of their clinical encounters audio-recorded over the course of project. We will determine before the site visits if residents are eligible to have a sample of their encounters audio-recorded. Clinicians who opt to participate will be sent a secure web link to a survey via email, so they can provide their age, gender, and years of experience post-fellowship (or year(s) of residency).

#### Randomization

The five participating sites were randomized by the project staff’s statistician, who was blinded to the identity of the sites, using R statistical software.

#### Pre-implementation phase

Prior to the start of the pre-implementation phase, stakeholders will complete the MORE survey. At the start of the pre-implementation phase, participating clinicians at each site will complete the ADOPT survey to indicate their attitude toward PDAs. We will audio-record five clinical encounters for each consenting participating clinician, and at the end of the study phase, we will conduct interviews with a convenience sample of clinicians and staff at each site to inform their completion of the NoMAD survey (see data collection section for details).

The Option Grid will not be used during the pre-implementation phase; however, patients will still complete the survey (see patient outcomes section for details) following their clinical encounters to provide baseline data for each site.

#### Active implementation phase

During each site’s active implementation phase, the uterine fibroid Option Grid PDA will be incorporated into the routine clinic workflow according to a tailored implementation strategy, as described in the “intervention” section above. Each site will keep a weekly record of the number of eligible patients who received the Option Grid (primary outcome).

As in the pre-implementation phase, patients will be asked to complete a survey (1) immediately following the clinical encounter and (2) 3 months after the clinical encounter.

Two months into the active implementation phase, research assistants at each site will begin audio-recording clinical encounters until each participating clinician (who consents to audio-recording) has had five of their encounters recorded. The audio-recordings will be sent to the project team at Dartmouth using a secure and HIPAA-compliant platform (Dartmouth Sharepoint). Two independent raters will assess (using the Observer Option-5 measure and fidelity checklist) the extent to which clinicians involve patients in the decision-making process using Option Grid tools. At the end of the active implementation phase, clinicians will complete the ADOPT survey, and we will conduct semi-structured interviews, guided by CFIR and NPT, with a convenience sample of participating clinicians to determine the tools’ utility, and the barriers and facilitators of their use in practice.

#### Sustainability phase

Prior to the sustainability phase, we will provide text and Picture Option Grid PDAs to each site. Project staff will limit communication with clinical sites throughout this phase to prevent unintended influence on continued PDA use. At the end of the sustainability phase, we will measure the number of eligible patients who receive the uterine fibroid Option Grid and clinician attitudes. We will also inquire about *if* and *how* study teams plan to use the text or Picture Option Grids after our study has ended, and we will assess the utility of the intervention from varied stakeholder perspectives at each site.

With the goal of offering guideline developers expertise on how to integrate shared decision-making processes into their documentation, we will contact organizations responsible for clinical practice guidelines regarding management of uterine fibroids. We will share the Option Grid and the evidence summaries created for the development of the existing tools, as well as indicating the new PCORI-generated evidence that we have considered in developing the PDA [41]. These steps will take place over the duration of the implementation study.

### Statistical analysis

#### Power calculation

The primary analysis has an expected sample size of 2600 patients across 30 to 40 clinicians (an estimated 87 patients per clinician [*n* = 30]) at each of the five sites. Because the intervention varies within clinician and our statistical models include clinician random and site-fixed effects, the relevant clustering variable is clinician-project week. With 40 project weeks and at least 30 clinicians, clustering is likely to have minimal impact on the results. Therefore, for a binary dependent variable (e.g., whether the uterine fibroid Option Grid is used or whether the patient gives a top **collabo**RATE score) with a baseline proportion of 0.5, a symmetric two-sided 95% confidence interval of width of at least 0.048 will have an 80% coverage probability of containing the true effect of the intervention, i.e., attaining a confidence margin of 0.048. In the context of shared decision making, such a margin is small and below typical levels of precision obtained from randomized studies.

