**Methods:**

We will conduct a randomized stepped-wedge implementation study where five sites will be randomized to implement the uterine fibroid Option Grid PDA in practice at different time points. Implementation will be guided by the Consolidated Framework for Implementation Research (CFIR) and Normalization Process Theory (NPT). There will be a 6-month pre-implementation phase, a 2-month initiation phase where participating clinicians will receive training and be introduced to the Option Grid PDAs (available in text, picture, or online formats), and a 6-month active implementation phase where clinicians will be expected to use the PDAs with patients who are assigned female sex at birth, are at least 18 years of age, speak fluent English or Spanish, and have new or recurrent symptoms of uterine fibroids. We will exclude postmenopausal patients. Our primary outcome measure is the number of eligible patients who receive the Option Grid PDAs. We will use logistic and linear regression analyses to compare binary and continuous quantitative outcome measures (including survey scores and Option Grid use) between the pre- and active implementation phases while adjusting for patient and clinician characteristics.

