## Methods

### Design

We will conduct a randomized stepped-wedge study where randomization of each site to a pre-implementation start date occurs prior to the start of the study (see Fig. 1 for details). The stepped-wedge design with a baseline pre-implementation phase allows for within-site pre/post comparisons. Following the pre-implementation phase, which occurs at a different time point for each site, we will provide a brief initiation session to introduce Option Grid PDAs and how to use them in practice. After initiation, clinicians will be expected to use the intervention in an “active implementation” phase. The SPIRIT checklist (see Additional file 1) guided our protocol development [20].

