#### Data analysis

Patient-level data will be clustered by site and clinician. Patients will be assigned to a single phase based on the date of their first encounter with a clinician at the site during the project period. Instances in which a patient has a repeated visit in the pre- and active implementation periods will be recorded to enable sensitivity analyses accounting for repeated observations.

Regression analyses will compare quantitative outcome measures (including survey scores and Option Grid use) between the pre- and active implementation phases while adjusting for patient and clinician characteristics. The extent to which clinicians involve patients in decision-making for each recorded encounter will be assessed by analyzing the Observer OPTION-5 and Option Grid fidelity checklist data from each phase of the study. We will conduct a framework analysis, guided by NPT, of the clinician interview transcripts to determine the barriers and facilitators of Option Grid implementation. Completion of the NoMAD Normalization Process Theory survey, based on interviews with site stakeholders, will enable us to make across-site assessments of implementation sustainability.

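### For secondary outcomes measured in both phases, the described pre-versus-active model names no calendar-time term, so residual secular trend is counted as implementation effect and the randomised stagger goes unused

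*Protocol article*

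**What the plan says.** The Design section of the protocol article states: "We will conduct a randomized stepped-wedge study where randomization of each site to a pre-implementation start date occurs prior to the start of the study". It then gives the use to which the design is put: "The stepped-wedge design with a baseline pre-implementation phase allows for within-site pre/post comparisons".

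The model is described in two places. The Power calculation section says that "our statistical models include clinician random and site-fixed effects". The Data analysis section says that regression will compare quantitative outcomes, survey scores and Option Grid use among them, "between the pre- and active implementation phases while adjusting for patient and clinician characteristics". The Abstract describes the same comparison and adjustment.

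Time enters the modelling text once, as a unit of clustering: "the relevant clustering variable is clinician-project week". Neither section names calendar month, quarter or period as a term for the mean.

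Table 2 lists the patient outcomes and Observer OPTION-5 under both the pre and the active phase. The section on the pre-implementation phase says the Option Grid is not used then.

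**The concern.** Each site moves in one direction, from pre through initiation to active. Within a site, and within a clinician, phase and time therefore rise together. Site fixed effects and clinician random effects remove differences between sites and between clinicians, but not a change over time that all of them share. A clustering unit that contains the week affects standard errors and leaves a trend in the mean where it was.

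A stepped wedge separates phase from time by having sites in different phases on the same date, and only a model containing calendar time uses those comparisons. Without one, the analysis is a before/after comparison at five sites, and the randomised start dates contribute nothing to it.

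What is at stake is the reading of the secondary outcomes. A background change in how clinicians discuss options, in the survey process or in the treatments on offer would be credited to the decision aid. The Background section makes the effect on clinical and other relevant outcomes a study aim.

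**Working it through.** **Inputs from the article**
- Phase lengths (Abstract): "There will be a 6-month pre-implementation phase, a 2-month initiation phase", then "a 6-month active implementation phase".
- Sample size (Power calculation): "The primary analysis has an expected sample size of 2600 patients across 30 to 40 clinicians". At about 87 patients per clinician with 30 clinicians, 2600/30 = 86.7, so 2600 is read as a total.
- Baseline proportion 0.5 and stated margin 0.048 (Power calculation).
- About 30% of eligible patients expected to complete the post-encounter survey (text with Table 2).
- Active-phase audio-recording starts two months into that phase (Secondary outcome measures).

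**Assumptions, not in the article:** equal split between phases, linear trend, even accrual, independent patients, the drifts of 0.25, 0.5 and 0.6 points per month, and a stagger of 1 to 4 months between sites (Fig. 1 was not available).

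**Step 1: the plan's own margin.** With 1300 per phase, SE = √(2 × 0.25/1300) = 0.0196.
- 95% half-width: 1.96 × 0.0196 = 0.038. Full width: 0.077.
- Difference detectable with 80% power, two-sided 5%: (1.96 + 0.84) × 0.0196 = 0.055.
- The same with a one-sided 5% test: (1.645 + 0.84) × 0.0196 = 0.049.

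The stated 0.048 is not recovered from its two-sided description; only the one-sided version comes close. The comparisons below therefore use 0.038 as the half-width of the model without time.

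**Step 2: time between phases.** Pre covers months 0–6 (midpoint 3) and active months 8–14 (midpoint 11). The gap is 11 − 3 = 8 months. For Observer OPTION-5, the active window is months 10–14 (midpoint 12); if recordings spread evenly over both windows, the gap is 12 − 3 = 9 months.

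**Step 3: bias with no true effect.** Bias = 8 × monthly slope:
- 0.25 points: 8 × 0.0025 = 0.020
- 0.5 points: 8 × 0.005 = 0.040
- 0.6 points: 8 × 0.006 = 0.048, the whole stated margin

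A least-squares fit with site effects only (5 sites, 12 site-months each) returned 0.040 for a slope of 0.005, as expected.

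**Step 4: type I error** = 1 − Φ(1.96 − bias/SE) + Φ(−1.96 − bias/SE).

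| Patients per phase | SE | drift 0.25/month | drift 0.5/month |
|---|---|---|---|
| 1300 | 0.0196 | 0.175 | 0.532 |
| 390 (30% of 2600, halved) | 0.0358 | 0.086 | 0.201 |

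A simulation with 30 clinicians of 87 patients, clinician effects and a 2-month stagger gave 17% and 54% at the larger size. Adding calendar-month effects returned the rate to about 4–6%.

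**Step 5: cost in precision,** same least-squares layout, 2600 patients.

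| Time term | Variance ratio to no time term | 95% half-width |
|---|---|---|
| none | 1 | 0.038 |
| linear | 6.5 | 0.098 |
| quarters | about 6–10 | about 0.09–0.12 |
| months | 7.7–13.9 | 0.107–0.143 |

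At 390 per phase each half-width is multiplied by √(1300/390) = 1.83: 0.070 with no time term and roughly 0.16–0.22 with quarters. Correlation within site and period would widen all of these further.

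**The case against.** The strongest reply is that the article does not set out a full model. The clause on random and fixed effects sits in the power paragraph as a reason for a remark about clustering, and it says what the models include, not all that they contain; the covariates appear only in the next section. An unseen SAP may add a period term. This stands as a limit: a reader might infer that the trial will be analysed without time, and the article does not establish that. But it does fix the contrast, the effects and the adjustment set, and it presents its precision as following from that model. If the SAP adds calendar time, the precision statement describes a different analysis.

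A reader might also infer that the primary analysis is compromised. The documents do not support this. Option Grid receipt is zero in the pre phase by design, so there is almost no background trend to mistake for effect.

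Three further points stand in part.
- Staffing change and resident turnover are partly absorbed by the clinician effects and by adjustment for clinician characteristics. Only the remaining trend matters.
- The drifts have no source in the article, and the survey denominator may be far below 2600, which lowers the false-positive rates.
- For Observer OPTION-5 the article says only that data from each phase will be analysed; it does not spell out a regression.

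Finally, with five sites the adjustment costs much precision, so there is a real trade of variance for bias. That supports reporting both models. It does not support presenting the unadjusted one as a randomised comparison.

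**Conclusion.** The point holds for secondary outcomes measured in both phases. The model as described attributes to implementation any trend the covariates do not explain, and makes no use of the randomised start dates.

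The 8-month gap follows from the article's own phase lengths; for Observer OPTION-5 it is longer, about 9 months under even recording. The multiplier of exactly 8 needs a linear trend and even accrual. The false-positive rates (17% and 53%, or 9% and 20% at the lower survey count) are illustrations at assumed drifts, not forecasts. The precision costs depend on an assumed stagger.

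The claim that type I error is uncontrolled should not be extended to the primary outcome.

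**What to change.** 1. In the SAP, name one form of calendar-time fixed effect, for example quarters, for the pre-versus-active models of these outcomes. Choose it before data are seen; switching form according to how the fit looks would bring in its own type I error.
2. Make the time-adjusted model the main estimate for these outcomes. Report the model without time beside it, labelled as a before/after analysis.
3. Restate the precision in the Power calculation section for these outcomes under the time-adjusted model, using the actual stagger and the expected number of survey respondents.

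Two considerations bear on the form. A linear term gave the same half-width (0.098) at every stagger tried, including none, so its precision comes from the straight-line assumption and not from the randomised starts. Quarter effects do use the stagger but leave some drift within a quarter: in the least-squares layout above, a drift of 0.5 points per month left 0.6 to 0.9 points of bias in place of 4.0. Month effects remove it, at the widest intervals.

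No new data are needed, because the date of first encounter already assigns each patient to a phase. The cost is the loss of precision in Step 5 of the check.

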### Participants

We will include physicians (attending or resident) who consent to participate in our implementation study and provide care to women with symptomatic uterine fibroids during the project duration at participating sites.

We will include patients showing new or recurrent symptoms of uterine fibroids (e.g., heavy menstrual bleeding, pelvic pressure or pain) who are seeking treatment and meet all of the following inclusion criteria: (i) assigned female sex at birth, (ii) at least 18 years of age, (iii) speak English or Spanish, and (iv) have the ability to complete short surveys online independent of assistance. We will not exclude pregnant patients. We will exclude postmenopausal patients because they may have different treatment options than those presented in the Option Grid PDA used in this study.

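### The power calculation takes the clinician-week as the cluster and dismisses clustering, but exposure changes once per clinician, so the 0.048 margin is unsupported

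*Protocol article*

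**What the plan says.** All of this is in the protocol article.

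- **Power calculation, size.** "The primary analysis has an expected sample size of 2600 patients across 30 to 40 clinicians", with "an estimated 87 patients per clinician" at n = 30. The same sentence then says that the clinician numbers apply to each of the five sites.
- **Power calculation, clustering.** The intervention varies within clinician and "our statistical models include clinician random and site-fixed effects", so "the relevant clustering variable is clinician-project week". From this the section concludes: "With 40 project weeks and at least 30 clinicians, clustering is likely to have minimal impact on the results". The next sentence opens with a therefore and gives a margin of 0.048 for a binary outcome "with a baseline proportion of 0.5". Option Grid use and top collaboRATE score are the two examples. No ICC or design effect is stated.
- **Abstract, Methods.** "There will be a 6-month pre-implementation phase, a 2-month initiation phase", followed by a 6-month active phase.
- **Pre-implementation phase.** The Option Grid is not used in this phase.
- **Primary outcome measure.** A paper grid reaches the patient when the clinician tears it from the pad.
- **Data analysis.** The comparison is pre-implementation against active phase, and patients are described as clustered within site and clinician. The clinician-week is not mentioned.

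**The concern.** A clinician effect that is constant over time removes only what is the same about a clinician in both phases. It does not remove differences in how much clinicians change when the tool arrives. Week-level clustering would be the right unit if exposure switched on and off from week to week. Here it switches once and then stays on for six months, so those differences do not average out over weeks.

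For Option Grid use the problem is plainest. Every clinician starts at zero, so there is no baseline level to subtract, and all between-clinician variation in active-phase uptake stays in the estimate. The study itself expects such variation: it measures clinician attitudes to decision aids, lets clinicians choose formats, and aims to find what goes with success and failure of implementation.

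At stake are the advertised precision and, if the analysis follows the same reasoning, the coverage of the reported intervals. The Power calculation and Data analysis sections also name different clustering units and need to be reconciled.

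**Working it through.** **Inputs from the article.** 2600 patients; 30 clinicians at 87 each (2600/30 = 86.7); 40 project weeks; proportion 0.5; margin 0.048.

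**Assumptions.** An equal split, 1300 per phase. ICC here means the share of variance due to clinician differences not shared between phases. The article gives none, so a range is shown. For uptake, 0.5 is used as the active-phase proportion, since the pre-phase proportion is zero.

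**1. The stated margin.** For two independent phases, SE = sqrt(2 × 0.25/1300) = 0.0196.
- 95% half-width: 1.96 × 0.0196 = 0.0384.
- Two-sided 5% with 80% power: 2.80 × 0.0196 = 0.0549.
- One-sided 5% with 80% power: 2.486 × 0.0196 = 0.0488.

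So 0.048 does not reproduce as a two-sided 95% figure with 80%. The nearest match is the one-sided calculation with a design effect of 1, which agrees with the claim of minimal impact.

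**2. What the choice of cluster does.** Design effect = 1 + (m − 1) × ICC.
- Clinician-week: m = 2600/(30 × 40) = 2.17, giving 1.01, 1.06 and 1.12 at ICC 0.01, 0.05 and 0.10. This is the source of the apparent minimal impact.
- Clinician-phase, 30 clinicians in total: m = 1300/30 = 43.3.
- Clinician-phase, 150 clinicians (30 at each of five sites): m = 1300/150 = 8.7.

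In the table, the two-phase half-width is 0.0384 × sqrt(design effect), the scaled margin is 0.048 × sqrt(design effect), and the uptake half-width is 1.96 × sqrt(0.25/1300 × design effect), which is 0.027 with no clustering.

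| Clinicians | ICC | Design effect | Two-phase half-width | 0.048 becomes | Uptake half-width |
|---|---|---|---|---|---|
| 30 | 0.01 | 1.42 | 0.046 | 0.057 | 0.032 |
| 30 | 0.05 | 3.12 | 0.068 | 0.085 | 0.048 |
| 30 | 0.10 | 5.23 | 0.088 | 0.110 | 0.062 |
| 30 | 0.20 | 9.47 | 0.118 | 0.148 | 0.084 |
| 150 | 0.01 | 1.08 | 0.040 | 0.050 | 0.028 |
| 150 | 0.05 | 1.38 | 0.045 | 0.056 | 0.032 |
| 150 | 0.10 | 1.77 | 0.051 | 0.064 | 0.036 |
| 150 | 0.20 | 2.53 | 0.061 | 0.076 | 0.043 |

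**3. Coverage if only a constant clinician effect is fitted.** Take 30 clinicians with 43 patients per phase. Each clinician's difference has sampling variance 2 × 0.25/43 = 0.01163. If the true effect varies between clinicians with SD τ, the variance is understated by the factor 1 + τ²/0.01163.
- τ = 0.05: factor 1.21; 1.96/sqrt(1.21) = 1.78; coverage about 92%.
- τ = 0.10: factor 1.86; 1.44; coverage about 85%.
- τ = 0.15: factor 2.93; 1.14; coverage about 75%.

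Simulation of the same layout gave 92%, 84% and 74%. A second simulation, for uptake, gave about 90%, 73% and 59% at ICC 0.01, 0.05 and 0.10, both for the clinician-intercept model and for standard errors clustered by clinician-week. Clustering by week therefore does not repair the coverage. Intervals built from clinician-level values held about 95% throughout.

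**The case against.** **The final intervals may be sound.** A reader might infer that the trial's confidence intervals will be too narrow. The article does not support that. It says the models have clinician random effects without saying that these are intercepts only, and the Data analysis section names the clinician as a clustering level. A clinician-by-phase term or clinician-clustered standard errors would be compatible with that and could sit in an analysis plan that is not shown. This objection stands: under-coverage is conditional on how the model is fitted.

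**The number of clinicians is unclear.** Read literally, 30 to 40 clinicians at each site means 150 to 200, and the effect is then much smaller. This also stands, although 87 patients per clinician fits only 30 in total.

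**The size rests on an unstated ICC and an ill-defined margin.** If 0.048 were a plain 95% half-width, it would leave room for a design effect of (0.048/0.0384)² = 1.56. That is exceeded only above ICC 0.56/42.3 = 0.013 with 30 clinicians, or 0.56/7.7 = 0.073 with 150. Likewise, uptake half-widths do not exceed 0.048 at ICC 0.05 or below. But the section states no such allowance and says that none is needed.

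**Two further inferences fail.**
- Because the study says "We will include physicians (attending or resident) who consent to participate", one might suppose that many clinicians contribute to one phase only. Nothing in the article says so, and eligible clinicians are identified before the pre-implementation phase.
- Forty project weeks against 6 + 6 months (about 52 weeks) looks inconsistent, but the project week is undefined and the timeline figure is not shown. It does not bear on clustering: more weeks would only make the clinician-weeks smaller.

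Conditioning on these five sites needs no separate caveat, since it already follows from the site fixed effects.

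**Conclusion.** The inference in the Power calculation section is wrong as written. The direction is certain whenever clinicians differ in how much they change, and for Option Grid use such differences are hard to avoid. The 0.048 margin is presented as following from that inference and has no other support.

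The size is not fixed by the article. On the reading that 87 patients per clinician implies (30 clinicians), it is material from ICC 0.01 upwards: design effects are about 1.4, 3.1 and 5.2 at 0.01, 0.05 and 0.10. With 150 clinicians it is modest, at about 1.1, 1.4 and 1.8. These figures assume 1300 patients per phase, equal numbers per clinician and a proportion of 0.5.

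The coverage figures of about 92%, 85% and 75% apply only with 30 clinicians, and only if the analysis uses nothing more than a clinician random intercept. Clustering by clinician-week would not prevent under-coverage either.

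**What to change.** - Delete the minimal-impact sentence and name the clinician, observed by phase, as the cluster, in agreement with the Data analysis section.
- Specify a clinician-by-phase random effect, or standard errors clustered by clinician with a small-sample t reference.
- State whether 30 to 40 clinicians is the total or the number per site, and make the patients per clinician agree with it.
- Restate the margin over an ICC range such as 0.01 to 0.20. Say whether it is a half-width or a detectable difference, and treat Option Grid use separately from collaboRATE because its pre-phase value is zero.

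The cost is wording plus one variance component or a change of standard error. No new data or design change is needed. The downside is a less favourable stated margin.

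### The precision statement contradicts itself (a 95% interval with 80% coverage), 0.048 matches no two-sided 95% quantity under an equal phase split, and the clinician count is unclear in scope

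*Protocol article*

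**What the plan says.** The only sample-size justification in the protocol article is the paragraph headed Power calculation. It opens: "The primary analysis has an expected sample size of 2600 patients across 30 to 40 clinicians", with "an estimated 87 patients per clinician" in parentheses for 30 clinicians, followed by "at each of the five sites". It takes clinician-project week as the relevant clustering unit and argues: "With 40 project weeks and at least 30 clinicians, clustering is likely to have minimal impact on the results".

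For a binary outcome "with a baseline proportion of 0.5", it then says that "a symmetric two-sided 95% confidence interval of width of at least 0.048 will have an 80% coverage probability of containing the true effect". The same sentence restates 0.048 as a confidence margin. The next sentence draws a conclusion from it: "In the context of shared decision making, such a margin is small", and below the precision that randomized studies usually achieve.

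The Data analysis section makes the comparison one of pre-implementation against active implementation. The abstract gives each of these phases as 6 months. The article does not state how the 2600 patients divide between them.

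**The concern.** Three things do not fit together.

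- **Confidence level and coverage.** Coverage probability is what a confidence level means. An interval cannot be a 95% interval and have 80% coverage. The 80% looks like a power figure, but the text does not say so.
- **Width and margin.** A margin is normally the half-width. Using one number for both leaves a factor of two open. The words setting 0.048 as a minimum width add to the difficulty, because a precision claim needs an upper bound.
- **Scope of the counts.** The closing phrase about the five sites may apply to clinicians, to patients or to both, and the patients-per-clinician figure agrees with only some of these readings.

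What is at stake is whether a reader can tell what the study can estimate or detect. The claim that the margin is small rests on this figure.

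**Working it through.** **Inputs.** From Power calculation: N = 2600, p = 0.5, two-sided 95%, 80%, 0.048, 30 to 40 clinicians, 40 project weeks, clustering of minimal impact (no design effect given). Assumed here: 1300 patients per phase, because the two phases are equally long.

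**Standard error of a difference in proportions.** SE = sqrt(0.25/1300 + 0.25/1300) = 0.0196.

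**Attempt to reproduce 0.048.**

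| Quantity | Formula | Result |
|---|---|---|
| 95% half-width | 1.960 × 0.01961 | 0.038 |
| 95% full width | 2 × 0.0384 | 0.077 |
| Detectable difference, two-sided 5%, 80% power | (1.960 + 0.842) × 0.01961 | 0.055 |
| Detectable difference, one-sided 5%, 80% power | (1.645 + 0.842) × 0.01961 | 0.049 |
| 80% interval, full width | 2 × 1.282 × 0.01961 | 0.050 |

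No two-sided 95% row gives 0.048. The one-sided detectable difference comes close, and so, less closely, does the full width of an 80% interval. Neither is what the sentence describes.

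**What 0.048 would mean.**

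- As ±0.048, coverage is 98.6%. As a total width of 0.048 (±0.024), it is 78%. Neither is 95%, and neither is exactly 80%.
- As a difference to detect, two-sided power is about 69%. Power of 80% would need about 3,400 patients in all.
- As the full width of a 95% interval, it would need N = (1.960/0.024)² = about 6,670.
- As a 95% half-width, it would need a design effect of (0.048/0.0384)² = 1.56. The plan's clusters average 2600/(30 × 40) = 2.2 patients per clinician-week. With equal cluster sizes, 1.56 implies an intracluster correlation of about 0.56/(2.17 − 1) = 0.48, which does not fit a claim of minimal impact.

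**Sensitivity to the split.**

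| Split | 95% half-width | Detectable difference (two-sided, 80% power) |
|---|---|---|
| 1:1 | 0.038 | 0.055 |
| 1:2 | 0.041 | 0.058 |
| 1:3 | 0.044 | 0.063 |
| 1:4 (520 and 2080) | 1.96 × 0.5 × sqrt(1/520 + 1/2080) = 0.048 | 2.802 × 0.02451 = 0.069 |

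So the half-width reaches 0.048 only at a split of about 1:4, which the article does not mention.

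**Clinician count.**

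- 2600/30 = 86.7, so 87 is right for 30 clinicians sharing 2600 patients.
- If 2600 is the study total and 30 to 40 clinicians work at each site, there are 150 to 200 clinicians: 2600/150 = 17.3 and 2600/200 = 13 patients each.
- If both counts are per site, 87 holds again, but N = 5 × 2600 = 13,000. The 95% half-width is then 1.960 × sqrt(0.5/6500) = 0.017 and the detectable difference 0.025, both further from 0.048.

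**The case against.** Several points on the other side stand.

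- A reader might infer that 0.048 matches no standard quantity at all. That goes too far: a one-sided 5% test with 80% power gives 0.049, and power at 0.048 is then 79%. It is tempting to conclude that this is where the number came from. The text says two-sided and names an interval, so the origin remains a guess.
- The equal split is this review's assumption. The 1:4 split above produces 0.048 as a half-width. It is hard to square with two 6-month phases, but the article does not exclude it.
- A reader might call 87 patients per clinician an arithmetic error, or say that it holds only for 30 clinicians overall. Neither is right. The division is correct, and it also holds if both counts are per site. The later reference to at least 30 clinicians suggests a study total, so the fault is the unclear scope of one phrase.
- A reader might infer that a five-fold uncertainty in patients per clinician overturns the argument about clustering. The plan's clustering unit is the clinician-project week. That averages about 2.2 patients with 30 clinicians and 2600/(150 × 40) = 0.4 with 150, so clusters are small on either reading.
- No recruitment target or decision rule in the article rests on 0.048. As a half-width it is conservative against 0.038; as a detectable difference it is optimistic by 0.7 percentage points (0.048 against 0.055).

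None of this rescues the sentence: the clash between 95% and 80%, and between width and margin, needs no assumption to see.

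**Conclusion.** The precision statement is wrong as written. The contradiction between confidence level and coverage, and the double use of 0.048, stand on the text alone.

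The numerical mismatch rests on 1300 patients per phase and no design effect. On that basis the two-sided 95% figures are 0.038 (half-width), 0.077 (full width) and 0.055 (detectable with 80% power), against the stated 0.048.

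The clinician count is a matter of unclear scope. It conflicts with 87 per clinician if 2600 is the study total and the clinician numbers are per site. No reading of the counts reconciles 87 and 0.048 with a two-sided 95% statement under an equal split.

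A reader might go on to infer that the study is too small. The document does not support that: it sets no target difference against which 0.038 or 0.055 could be judged inadequate.

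**What to change.** 1. Replace the sentence with one coherent statement that gives the phase split, sidedness and power. For example: with 1300 patients per phase and p = 0.5, before clustering, the two-sided 95% confidence interval has a half-width of 0.038, and the difference detectable with 80% power is 0.055. If another split or a one-sided criterion was intended, say so and give the matching figures.
2. State any design effect assumed for the clinician-project week, and multiply the half-width and the detectable difference by its square root (not by the design effect itself).
3. Say whether 2600 patients and 30 to 40 clinicians are study totals or per site, and make patients per clinician agree.
4. Rest the conclusion that the margin is small on the restated figure.

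The cost is wording and restated figures; design, data collection and analysis are untouched.
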